**2.2.7.3**

Clinical endpoints

Index admission:

1.total death

2. Cardiac death

3. Non-index procedure myocardial infarction

4. Stent thrombosis (definite and probable)

5. TLR and TVR

6. non-TVR

Follow up:

1. Total death

2. Cardiac death

3. Non-index procedure myocardial infarction

4. Stent thrombosis (definite and probarble)

5. TLR and TVR

6. non-TVR

7. CCS angina class

8. Vascular cerebral events

9. Admissions for congestive heart failure or arrhythmia

**2.2.8 Endpoints definitions: OCT**

Follows definitions from the “Consensus Standards for Acquisition, Measurement, and Reporting of Intravascular Optical Coherence Tomography Studies” paper by Tearney et al. JACC 2012

- - Segments to follow definitions in coming consensus standards
- Quantitative measurements
  - Segments to follow definitions in coming consensus standards
- Primary endpoint is Coronary Healing Score, see 2.2.6 for definition.

**2.2.9 Defination of endpoints (clinical)**

#### 2.2.9.1 All cause death (total death)

Total death encompasses cardiac death and other fatal categories, which include cerebrovascular death, death from other cardiovascular disease (i.e. pulmonary embolism, dissection aortic aneurysm will be included in this category), death from malignant disease, death from suicide, violence or accident, or death from other reasons.

#### 2.2.9.2 Cardiac death

Cardiac death encompasses coronary heart disease death including fatal myocardial infarction, sudden cardiac death including fatal arrhythmias and cardiac arrest without successful resuscitation, death from heart failure including cardiogenic shock, and death related to a cardiac procedure or surgery within 28 days from the procedure.

#### 2.2.9.3 Non-procedure related myocardial infarction

The term myocardial infarction should be used when there is evidence of myocardial necrosis in a clinical setting consistent with myocardial ischemia. Under these conditions any one of the following criteria meets the diagnosis for myocardial infarction (11):

1) Detection of rise and/or fall of preferably troponin T with at least one value above the 99th percentile of the upper reference limit (URL) together with evidence of myocardial ischemia with at least one of the following (MI types 1 or 2):

a. Symptoms of ischemia

b. ECG changes indicative of new ischemia (new ST-T changes or new LBBB)

c. Development of pathological Q waves in the ECG

d. Imaging evidence of new loss of viable myocardium or new regional wall motion abnormality

2) Sudden, unexpected cardiac death, involving cardiac arrest, often with symptoms suggestive of myocardial ischemia, and accompanied by presumably new ST elevation, or new LBBB, and/or evidence of fresh thrombus by coronary angiography and/or at autopsy, but death occurring before blood samples could be obtained, or at a time before the appearance of cardiac biomarkers in the blood (MI type 3).

3) Pathological findings of an acute myocardial infarction.

#### 2.2.9.4 Procedure related biochemical release of markers (Myocardial Infarction related to the Index Procedure)

The following biomarkers may be used in the study: CK-MB mass and/or Troponin-T/-I. For percutaneous coronary interventions (PCI) in patients with normal baseline biomarker values, elevations of cardiac biomarkers greater than 5 X 99th percentile URL are designated as defining PCI-related myocardial infarction (MI type 4a). If cardiac troponin is elevated before the procedure and not stable for at least two samples 6 hours apart, there are insufficient data to recommend biomarker criteria for the diagnosis of peri-procedural myocardial infarction. If the values are stable or falling, criteria for re infarction by further measurement of biomarkers can be applied; that is 20% or more increase of the value in the second sample after the procedure. This value should also exceed the 99th percentile URL .

#### 2.2.9.5 Target lesion revascularization

Coronary artery bypass grafting with grafting or PCI of index lesion.

#### 2.2.9.6 Target vessel revascularization

Coronary artery bypass grafting with grafting or PCI of index vessel.

#### 2.2.9.7 Stent thrombosis

Stent thrombosis is recognized when documented by angiography and/or autopsy and when meeting the criteria for spontaneous myocardial infarction occurring in the territory of the treated vessel (11). Stent thrombosis are categorized as acute, sub-acute, late and very late and as definite, probable and possible according to the ARC-criteria (12).

**2.2.10 Biochemical analysis**

**2.2.10.1** Creatinin, hemoglobin, Troponin T will be analyzed during index procedure post procedure and at 12 months follow up. ProBNP will be analyzed at 12 months follow-up

**2.2.10.2** Plasma will be drawn immediately after the procedure and frozen in a bio bank for later analysis.

**2.2.10.3** Blood from target vessel will be drawn for analysis of markers of myocardial necrosis from thrombus aspiration catheter.

**2.1.10.4** Visibible thrombus aspirates will be sent for analysis at Amsterdam Medical Center.

**2.2.11** **Optical coherence tomography core lab**

### OCT off line analysis is performed at the Interventional Imaging Core Laboratories at the Department of Cardiology Aarhus University Hospital, Skejby, Aarhus, Denmark. All files to be transferred on CD´s or DVD´s in RAW format.

### 2.2.12 OCT acquisition technique

### OPTIS St. Jude Medical OCT system will be used. Pre PCI: (after predilatation) OCT imaging catheters will be inserted and advanced to a position distal to the lesion and acquisition of the lesion will be performed at 36 mm/s (OPTIS). Final result acquisition: the OCT imaging catheters will be inserted and advanced to a position with acquisition start at least 5 mm distal to the distal stent edge. Pullback speed 20 mm/sec covering the. If target segment is longer than 53 mm then an additional pullback is performed covering entire target area. Final result is acquired by OCT. Flushing is performed by automated injector or manual injection. Iomerone contrast will be used for flushing. In case of difficult flushing, a larger guiding catheter or a more co-axial position of the guiding catheter is recommended. OCT files from baseline, follow-up and events (pre-intervention) should be submitted in RAW format to the Interventional Imaging Core Laboratory at Aarhus University Hospital via the study organization. Flushing for 3 seconds of the OCT imaging wire immediately before each pullback is mandatory

Careful evaluation of acquired pullback before finalizing procedure:

- Blood in catheter?
- Insufficiently flushed vessel?
- Target area acquired?
- SB ostium visible? (excess wire shadow?)

REPEAT PULLBACK IF QUALITY IS INSUFFICIENT

**2.3 Treatment step-by-step**

Before arrival et cath lab, loading with acetylic salisylic acid and one of the antiplatelet agents clopigrogel/pragusgrel/ticagrelor is mandatory. Heparin or bivalirudin at start of procedure. After angiography and confirmation of presence of thrombus GpIIb/IIIa inhibitors are administered at operators discretion.

After thrombus aspiration with TIMI flow 2 or more the patient will be asked to participate in the study. Oral consent witnessed by staff non-affiliated with the study will be obtained.

OCT scan will be performed after 0.2 mg intracoronary nitroglycerine for sizing and lesion evaluation. The patient is then randomized into one of two arms in a 1:1 distribution:

1. Direct stenting with everolimus eluting stent
2. Direct stenting with bioresorbable stent

Direct stenting is the preferred method of implantation to keep procedure as short and simple as possible. Predilatation will not considered protocol violation if deemed necessary by operator. After stenting and post dilation at operator’s discretion, a second OCT will be performed. Any further post dilatation will be performed at operator’s discretion. A final OCT will be done if further postdilatation is performed. 0.2 mg intracoronary nitroglycerine is administered before each OCT scan.

Patient will be asked to sign an informed consent after the procedure (<24 hrs).

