Metallic drug eluting stents are being challenged by new stents made from biodegradable platforms, or BVS (Biodegradable Vascular Scaffold). The Absorb BVS (Abbott Vascular, Santa Clara, CA) is the first of these being commercially available in Norway. The second-generation Absorb BVS is a balloon-expandable device consisting of a polymer backbone of poly-l-lactide (PLLA) coated with a thin layer of a 1:1 mixture of an amorphous matrix of poly-d, l-lactide (PDLLA) polymer and 100 μg/cm^2^ of the antiproliferative drug everolimus. Two platinum markers located at each Absorb BVS edge allow for accurate visualization of the radiolucent Absorb BVS during angiography or other imaging modalities. The PDLLA controls the release of everolimus, 80% of which is eluted within the first 30 days. Both PLLA and PDLLA are fully bioresorbable. The polymers are degraded via hydrolysis of the ester bonds, and the resulting lactate and its oligomers are quickly transformed to pyruvate and metabolized in the Krebs energy cycle. Small particles, less than 2 μm in diameter, have also been shown to be phagocytized and degraded by macrophages. According to preclinical studies, the time for complete bioresorption of the polymer backbone is 2 to 3 years It has been proven to be safe and non-inferior to metallic everolimus stents in the ABSORB II, kohort B trial [7, 8]. The bioresorbable scaffold has obvious advantages over metallic, as it will not hinder any future revascularization. However there are concerns regarding the strength of the scaffold. It is therefore recommended with more rigorous lesion preparation, using balloons for predilatation. Currently only one small study has been published studying specifically BVS in STEMI patients. This study is not randomized and does not address the issue of predilatation[9].

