**Rationale**

The pathological analysis will be compared to pre-,post- PCI and follow-up OCT readings to establish if composition, size and age predicts residual thrombus pre PCI as measured stent result after PCI and primary and primary endpoint at follow-up as measured by OCT. These results will be published in a separate substudy paper.

- 1. **Study goals and objectives**

Study goal is to compare the performance of the Absorb bioresorbable scaffold with a metallic drug eltuting stent in the STEMI patient.

Hypothesis is that a bioresorbable vascular scaffold (BVS) is non-inferior to standard of care, eg. direct stenting with metallic DES, using direct stenting after thrombus aspiration.

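### The protocol contradicts itself on whether and when predilatation occurs, so the randomised comparison does not support the direct-stenting conclusion that the hypothesis names

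*Protocol*

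**What the plan says.** Four places in the protocol bear on predilatation.

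- **Study goals and objectives (section 1).** The goal is a general comparison of the two devices in STEMI. The hypothesis is narrower: BVS is non-inferior to standard care, described as "direct stenting with metallic DES, using direct stenting after thrombus aspiration".
- **New stent platforms (section 1, background).** Because of concerns about the strength of the scaffold, the text says of BVS: "It is therefore recommended with more rigorous lesion preparation, using balloons for predilatation". It makes no such statement for metallic stents.
- **Section 2.2.12, OCT acquisition.** The first scan is described as "Pre PCI: (after predilatation) OCT imaging catheters will be inserted".
- **Section 2.3, treatment step by step.** The order is aspiration, oral consent, an OCT scan for sizing and lesion evaluation, then 1:1 randomisation to "Direct stenting with everolimus eluting stent" or "Direct stenting with bioresorbable stent". After the arms are listed, the text says "Direct stenting is the preferred method of implantation to keep procedure as short and simple as possible", followed by "Predilatation will not considered protocol violation if deemed necessary by operator". No criteria for necessity are given.

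Section 2.0 states that the trial is not blinded. Section 3.4 plans intention-to-treat for the primary endpoint and a per-protocol analysis of actual treatment. No analysis is defined by whether direct stenting was achieved.

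**The concern.** The hypothesis and arm labels fix an implantation technique that the procedure leaves open. On the order in section 2.3, the choice to predilate is made by an operator who knows the device, and the protocol's own background supplies a reason to predilate one device and not the other. If use then differs by arm, the contrast is between each device together with its lesion preparation, while the stated conclusion would be about the devices under direct stenting.

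The protocol also does not settle whether predilatation comes before or after allocation. This matters statistically. Predilatation before allocation cannot depend on the arm; predilatation after open allocation can. What the trial may conclude about technique depends on which order is meant.

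**Working it through.** **Step 1. Set the passages side by side.**

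| Place | Is predilatation part of the procedure? | When, relative to randomisation? |
|---|---|---|
| Hypothesis (section 1) | No; direct stenting is named | Not applicable |
| Background on BVS (section 1) | Recommended for BVS | Not stated |
| Section 2.2.12 | Taken as already done at the pre-PCI scan | Before, because section 2.3 randomises after that scan |
| Section 2.3 | Not preferred, but allowed in either arm if judged necessary | Mentioned only after allocation |

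Section 2.3 has only one scan before stenting, so the pre-PCI scan of section 2.2.12 must be that one. The two operative sections therefore conflict on timing. Section 2.2.12 also conflicts with the direct-stenting label of both arms.

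**Step 2. What each planned analysis can show.**

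- Intention-to-treat compares the arms as randomised under one common rule: direct stenting preferred, predilatation allowed. That is a valid comparison of two strategies. It is not a comparison with the technique held fixed.
- The analysis by actual treatment most naturally sorts patients by device received. Predilatation judged necessary is not a violation, so predilated patients stay in. This analysis does not isolate direct stenting either.

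**Step 3. Reproduce the plan's figure.** Inputs from section 3.3: SD 1.39 mm2, margin 0.72 mm2, alpha 0.05, power 0.85, true difference taken as 0.

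n per arm = 2 × [1.39 × (1.645 + 1.036) / 0.72]² = 53.6, rounded up to 54. This matches the protocol with alpha read as one-sided 5%. One-sided 2.5% would give 67. The standard error of the difference is 1.39 × √(2/54) = 0.268 mm2, and power at 54 per arm is 0.852. Nothing here disputes the figure of 54.

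**Step 4. Illustrate the size.** The protocol gives no predilatation rates and no effect of predilatation on minimum flow area (MinFA). The inputs below are assumptions: 10% predilated with DES, 30% to 70% with BVS, and an effect of 0.2 to 0.5 mm2 in either direction.

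Shift in the arm contrast = (difference in share predilated) × (effect on MinFA).

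- Low: (0.30 − 0.10) × 0.2 = 0.04 mm2, and 0.04/0.72 = 6% of the margin.
- High: (0.70 − 0.10) × 0.5 = 0.30 mm2, and 0.30/0.72 = 42% of the margin.

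For the narrower question of the devices under direct stenting, at 54 per arm and one-sided 5%:

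- If the shift favours BVS and the true direct-stenting difference equals the margin, the chance of declaring non-inferiority is 1 − Φ(1.645 − shift/0.268). This gives about 7% at 0.04 mm2 and 30% at 0.30 mm2, instead of 5%.
- If the shift goes against BVS and there is no true difference, power is Φ((0.72 − shift)/0.268 − 1.645). This gives about 82% and 47%, instead of 85%.

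MinFA is used because it is the only measure with a stated margin. The declared primary endpoint is the Coronary Stent Healing Index, for which no comparable calculation is possible from the protocol.

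**The case against.** The strongest reply is that this is a sound pragmatic device comparison. The study goal is simply to compare the two devices, the rule in section 2.3 is the same for both arms, and lesion preparation that follows from the device belongs to the device strategy. Randomisation is not broken by it. All of this stands, and it limits the point to what may be concluded about direct stenting.

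Several stronger readings are tempting and are not supported:

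- *The trial question cannot be answered.* Intention-to-treat answers the general question of the stated goal. Only the direct-stenting version goes unanswered.
- *Technique differs by arm.* No rate appears in the protocol. Unequal use is a foreseeable risk, not a stated fact.
- *Predilatation is recommended for BVS only, by trial rule.* The recommendation is background. The operative rule makes no distinction by arm.
- *Predilatation is never a violation.* The text makes this conditional on the operator judging it necessary, though without criteria the condition limits little.
- *Predilatation is decided after open allocation.* Section 2.3 reads that way, but section 2.2.12 implies the opposite.
- *The planned analysis drops the harder lesions from the BVS arm.* No section plans an analysis restricted to directly stented patients. Such a restriction would be a later misuse, not a flaw in a planned analysis.

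It is also fair that the illustrated sizes rest on assumptions throughout, that even the sign is unknown, and that they are on MinFA and not on the primary endpoint.

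**Conclusion.** The point holds as an internal contradiction with a consequence for the conclusion. The hypothesis and arm labels name direct stenting, section 2.3 makes it a preference with discretion and no criteria, and sections 2.2.12 and 2.3 disagree on whether predilatation precedes or follows allocation. The trial can conclude on BVS versus DES with direct stenting preferred and predilatation allowed. It cannot, from its planned analyses, conclude on the devices under direct stenting alone.

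The contradiction is certain from the text; the numerical effect is not. The range of 0.04 to 0.30 mm2 (6% to 42% of the margin) depends entirely on the assumed rates and effects, and its direction is open. The stated sample size is unaffected.

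**What to change.** 1. Reconcile the background on BVS, the hypothesis, section 2.2.12 and section 2.3 on whether predilatation occurs and when it occurs relative to the pre-PCI OCT and to randomisation. Which clinical rule applies is for the sponsor.
2. If operator discretion stays, reword the hypothesis and the intended conclusion as BVS versus DES with lesion preparation at operator discretion.
3. Record pre- and post-dilatation for every patient and report both by arm.
4. State that no direct-stenting claim will be drawn from a subset defined by what was done after allocation.

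The cost is a few sentences and the recording of two procedural items. The small downside is a broader stated hypothesis.

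Recording intended predilatation before allocation and basing a direct-stenting claim on the patients marked no is a possible addition, but it is debatable. Intent may depend on the device, patients marked no may still be predilated, and the group shrinks. If 10% to 50% were marked yes (an assumption), 54 per arm becomes about 49 to 27, and power on the inputs of section 3.3 falls from 85% to about 82% to 60%.

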**2.4 Antiplatelet therapy**

12 months dobble platelet therapy (DAPT) with acetylic salisylic acid and either ticagrelor or prasugrel.

**2.5 Multi vessel disease**

This is a single vessel disease study. Should other lesions need treatment at index hospitalization, the use of everolimus DES is recommended.

**2.6 Angiographic and OCT follow-up**

After 12 (± 1) months a diagnostic angiography by femoral or radial route will be performed and the projections used at the index angiography will be repeated after 0.2 mg intracoronary nitroglycerine. OCT acquisition is performed by 6F guiding catheter or larger.

In case of angiographic stenosis, revascularization should only be performed if FFR<0.8 or other objective proof of ischemia has been acquired.

The 12 months follow-up angiograms and the OCT runs will be stored on CDs and sent by mail to the Core Laboratory for Interventional Imaging angiographic core laboratories.

In case of any target lesion revascularization before 12 months a coronary angiogram and OCT should be performed.

**3.0 Data management and statistical analysis**

**3.1 Primary endpoint**

The primary endpoint in the two groups will be analyzed on patient level using paired t-test. A p-value considered indicating significance will be 5%.

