**2.2.6 Primary endpoint**

Coronary Stent Healing Index (cumulated):

1. Uncovered struts: 2% =1 – 5% =2 – 10% =3 - 15% =4 – 20% =5 – 25% =6 – 30% =7 – 35% =8 – 40% =9

2)    Uncovered struts in fornt of side branch on acquired or persistent malapposed struts. 10% =1 – 20% =2 – 30% =3 etc… til 100%=10

3)     Persistent malapposition: ≥2 nabo struts længde mindst 1 mm =1 ; ≥2mm=3 ; ≥3 mm = 3

4)     Acquired malapposition: ≥2 adjacent struts of at least 1 mm length  =2 ; ≥2mm=4 ; ≥3 mm = 6

5)     Neointimal thickness in one frame >200 =1 - >300 =2  - >400 =3 or diameter stenosis >50% =4 - > 75% =5

6)      Cumulated extra stent lumen increase in match cross sectional analysis: (gns. areal mål): ≥0.2mm2 =1 ; ≥0.4 mm2 = 2; ≥0.6mm2=3 ; ≥0.8 mm2 = 4 ;  ≥1.0 mm2=5 ; ≥1.2 mm2 = 6

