**3.2 Secondary endpoints and other variables**

Differences in categorical variables between the two groups will be analyzed using the chi-square test or Fisher´s exact test. Continuous variables will be analyzed using independent sample t-test and Mann-Whitney U-test, and time to event data will be analyzed using the Kaplan-Meier method and the log-rank test. OCT and angiographic parameters will be evaluated by Spearman correlation analysis. Binary logistic-regression analysis will be performed to identify independent predictors of difference in outcome. Pre and post PCI OCT of vessel size, lesion severity, lesion length. All p-values are two-sided. Level of significance is 5%. The analysis is performed on an intention to treat basis and by actual treatment.

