**4. Randomization and data management**

**4.1 Randomization**

The participants will be randomized using online randomization tool provided by TrialPartner.

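### Section 3.1 compares two independently randomised arms with a paired t-test; no pairs exist, so the primary p-value depends on row order and cannot be computed when the arms differ in size

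*Protocol*

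**What the plan says.** Section 3.1 of the protocol gives the primary analysis in one sentence: "The primary endpoint in the two groups will be analyzed on patient level using paired t-test". The next sentence sets the significance level at 5%.

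The design is described elsewhere:

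- Section 2.3, on allocation: "The patient is then randomized into one of two arms in a 1:1 distribution".
- Section 4.1, on method: "The participants will be randomized using online randomization tool provided by TrialPartner". No matching, crossover or within-patient control is described.
- Section 2.5: "This is a single vessel disease study". Section 2.2.6 defines the primary endpoint as a cumulated index, which gives one score per patient.
- Section 3.2, for the secondary endpoints and other variables: "Continuous variables will be analyzed using independent sample t-test and Mann-Whitney U-test".

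Section 3.3 derives 54 patients per group from an SD of 1.39 mm² and a non-inferiority margin of 0.72 mm² for minimum flow area, with alpha 0.05 and power 0.85.

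**The concern.** A paired t-test analyses differences within pairs that the design has created: the same patient measured twice, or matched patients. Here each score in one arm belongs to a patient with no designated partner in the other arm. To run the test, the analyst must supply a pairing that the protocol does not define, and different pairings of the same data give different p-values.

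The test also needs equal numbers in the two arms. The endpoint requires OCT at 12 months. Sections 11.3 and 11.4 let patients decline the follow-up angiogram, withdraw, or be lost to follow-up, so unequal evaluable numbers should be expected. The analyst would then either drop valid primary-endpoint data, which sits badly with the intention-to-treat analysis in section 3.4, or depart from the protocol after the data are in. The trial is open label and section 4.2 says the core laboratory is not blinded, so an unspecified choice in the primary analysis is especially unwelcome.

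**Working it through.** **1. Could any reading create pairs?** The sentence in 3.1 concerns the two groups at patient level, so it is a between-arm comparison. Items 3, 4 and 6 of the index in 2.2.6 (persistent malapposition, acquired malapposition, lumen increase in matched cross-sections) draw on baseline and follow-up OCT. They still feed one score per patient and link nobody across arms. Bailout stenting (section 9) creates no pairs either.

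**2. The plan's own sample size.** Inputs from 3.3: SD 1.39, margin 0.72, power 0.85, alpha 0.05 (taken as one-sided), assumed true difference 0.

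n per arm = 2 × SD² × (z₀.₉₅ + z₀.₈₅)² / margin² = 2 × 1.39² × (1.645 + 1.036)² / 0.72² = 53.6, so 54.

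This is the stated figure. At one-sided 0.025 the result is 66.9, so 67, which does not match. The variance term 2 × SD² is that of two uncorrelated groups. A paired design would use 2 × SD² × (1 − ρ), and no ρ is given. The trial was therefore sized with no credit for pairing.

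**3. Why row order matters.** The mean difference is the same under every pairing, but its standard error is not. The paired test uses the variance s₁² + s₂² − 2·r·s₁·s₂, where r is the correlation produced by whichever pairing is used. With equal SDs, the paired t statistic is the independent t divided by √(1 − r). Degrees of freedom fall from 2 × 54 − 2 = 106 to 54 − 1 = 53.

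Under random ordering, r has mean 0 and SD 1/√53 = 0.137, so about 95% of orderings give r between −0.269 and +0.269. Take data with an independent p of exactly 0.050, so t = 1.983 on 106 df:

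| r from the ordering | paired t | paired p (53 df) |
|---|---|---|
| +0.269 | 1.983 / 0.855 = 2.319 | 0.024 |
| 0 | 1.983 | 0.053 |
| −0.269 | 1.983 / 1.127 = 1.760 | 0.084 |

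The paired p falls below 0.05 when the paired t exceeds 2.006, that is, when r > 1 − (1.983/2.006)² = 0.023. That happens in about 43% of orderings.

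**4. Simulation.** Re-ordering one arm of such a data set 20,000 times gave a central 95% range of 0.024 to 0.084, a median of 0.053, and 43% of orderings below 0.05, in agreement with step 3.

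A second data set was less borderline (54 per arm, SD 1.39, assumed true difference 0.5, independent p = 0.0128). Its paired p-values ran from 0.0007 to 0.043, with a central 95% range of 0.0046 to 0.0286. All stayed below 0.05.

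**5. Error rates under random pairing, equal arms.** Two-sided type I error was 0.0497 paired against 0.0500 independent (100,000 simulated trials of 54 per arm). Power for a 0.72 mm² difference at one-sided 0.05 is 0.844 paired against 0.848 independent.

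**6. Unequal arms.** With 54 against 52 evaluable patients the paired test cannot be computed.

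**The case against.** The best counter-argument is that this is a slip of wording with modest numerical consequences. If the pairing is chosen without sight of the data, the test keeps its 5% level and loses about 0.4 percentage points of power. Halving the degrees of freedom sounds worse than it is. The 43% figure comes from a data set placed exactly on the threshold. With an independent p of 0.10, only about 1% of orderings are significant; at 0.20, none; at 0.0128, all. Over repeated trials of 54 per arm, the two tests disagree at the 5% level in about 1.2% of trials with no true difference and about 4% with a difference of 0.36 SD. With unequal arms the procedure simply fails, so the mistake would probably be noticed. Section 3.2 and the sample size already point to an independent comparison.

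All of that is correct, and it limits the claim: the harm is not a false-positive rate above 5%, and the conclusion would change only in borderline results. It does not rescue the sentence. The protocol states the wrong test outright, and a separate analysis plan naming another test would contradict it on the primary analysis. Noticing the problem at analysis means choosing the primary test after the data are available. That the sponsor probably intended an unpaired test is a reason to write it.

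**Conclusion.** The concern holds. Section 3.1 prescribes a test whose required structure is absent from the design, and it conflicts with the test named in section 3.2 and with the uncorrelated-groups variance used in 3.3. The primary p-value depends on an ordering that the protocol does not fix: at an independent p of 0.050, the central 95% of orderings run from 0.024 to 0.084. The test cannot be run with unequal evaluable arms. The figures assume 54 evaluable patients per arm, and the simulations use normally distributed outcomes with equal SDs. The range and the 43% describe a borderline result, not the typical one. Type I error stays near 5% under data-blind pairing. Because this sentence governs the trial's main conclusion, it must be corrected before analysis.

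Two neighbouring problems are separate from this one. The only non-inferiority margin is stated for minimum flow area, not for the healing index. The 54 per arm needs one-sided 0.05, whereas section 3.2 says "All p-values are two-sided".

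**What to change.** In section 3.1, replace the paired t-test with an independent two-sample comparison of the healing index. Report the between-arm mean difference with its confidence interval, from an unequal-variance (Welch) t-test or a linear model with treatment arm as a term. The independent-samples t-test already named in section 3.2 would also cure this defect. All evaluable patients in both arms are then used, whatever the arm sizes. A paired test would be appropriate only for within-patient change from baseline to 12 months, if such an analysis is added.

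The cost is one sentence in the protocol, carried into any analysis plan, with no operational change. The 54 per arm stands under the assumptions of section 3.3. This correction does not supply the missing margin for the index, which has to be settled on its own.
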